# Community-based intervention for cervical cancer screening uptake in a semi-urban area of Pokhara Metropolitan, Nepal (COBIN-C): study protocol for a cluster-randomized controlled trial

**DOI:** 10.1186/s13063-021-05049-3

**Published:** 2021-01-26

**Keywords:** Female community health volunteers, Community health worker, Non-communicable diseases, Cervical cancer screening, Community-based, Randomized controlled trial, Nepal

## Abstract

**Background:**

Previous studies suggest that health intervention designed to increase cervical cancer screening has been effective to reduce cervical cancer incidence and mortality. The aim of this study is to determine the effect of a home-based health education intervention for increasing cervical cancer screening uptake delivered by trained female community health volunteers (FCHVs), a category of community health worker in Nepal.

**Methods:**

A community-based, open-label, two-armed, cluster-randomized trial [seven clusters (geographical wards) randomized for the intervention, and seven for the control arm]. The participants are recruited from a population-based survey with a sample size of 884. Based on population proportion size, 277 women will be recruited for the intervention group and 413 women recruited for the control group. A 12-month community-based health education intervention will be administered mobilizing the FCHVs, based on the Health Belief Model. The primary outcome measure of the study will be the difference in percentage of cervical cancer screening uptake between the two study arms. The primary outcomes will be modeled by using mixed-effect logistic regression analysis.

**Discussion:**

COBIN-C is the first study investigating the effect of a community-based health education intervention by FCHVs on increasing cervical cancer screening uptake among women in Nepal. The purpose of this study is to develop and implement a home-based, culturally sensitive program to increase cervical cancer screening coverage at the community level.

**Trial registration:**

ClinicalTrials.gov NCT03808064. Registered on January 14, 2019.

**Supplementary Information:**

The online version contains supplementary material available at 10.1186/s13063-021-05049-3.

## Background

Cervical cancer is a common cancer among women in most low- and middle-income countries (LMICs) in Asia, Africa, and Latin America [1]. It is the major cause of cancer deaths among women in Nepal with an estimated 2942 new cases and 1928 deaths in 2018 [1]. Screening is one of the most effective tools for early diagnosis, prevention, and treatment [2, 3]. However, there are very limited tools and skilled health professionals available for cervical cancer screening in many LMICs, including Nepal. The World Health Organization (WHO) and the Alliance for Cervical Cancer Prevention (ACCP) recommend that countries, areas, or institutions seeking to initiate or strengthen cervical cancer screening programs should consider introducing or expanding visual inspection with acetic acid (VIA) until more appropriate and affordable HPV-based tests become available [4, 5]. A single-visit approach with VIA and cryotherapy has been shown to be a safe, acceptable, feasible and is a potentially efficient method of cervical cancer prevention in Nepal [6]. National guidelines for the prevention and screening of cervical cancer includes VIA as a screening method for cervical cancer [7]. Studies reveal that participation of Nepalese women for cervical cancer screening is still low [2.8% (25–64 years); 1.5% (15–49 years); 5.4% (30–65 years)] [8–10]. Thus, there is a need for appropriate, cost-effective, and sustainable interventions to increase VIA screening uptake at the primary health care level across Nepal.

Studies suggest that mobilizing lay health workers and empowering them with integrated training could contribute in expansion of the knowledge base on non-communicable diseases (NCDs) at the community level and harmonize the community-based interventions [11–13]. In Nepal, female community health volunteers (FCHVs) have carried out community-based public health initiatives for more than 25 years and are willing to contribute to help mitigate NCDs [14]. FCHVs, a category of community health workers in Nepal, are married women, locally selected and trained through the Ministry of Health and Population. Previous studies demonstrated that FCHVs are able to screen for diabetes and hypertension: this has provided a favorable platform to explore the possible roles of FCHVs for increasing cervical cancer screening uptake [15, 16].

Mobilizing FCHVs to educate women and encourage them to participate in cervical cancer screening, and thus strengthening grass root level primary health provision, could be an acceptable and culturally appropriate intervention, which needs to be tested. Furthermore, it may contribute in the implementation of the National Cervical Cancer Screening and Prevention policy and ultimately help to reduce cervical cancer mortality in Nepal. The health promotion package will be a simple, feasible and effective approach.

In our study, we will conduct a community based cluster-randomized controlled trial (cRCT) to explore the roles of FCHVs in educating and empowering women through home visits to increase the uptake of VIA screening. Therefore, the primary outcome of the study is to increase the cervical cancer-screening uptake in the study area.

## Methods

This manuscript adheres to the Consolidated Standards of Reporting Trials (CONSORT) 2010 statement: extension to cRCT [17].

### Study design and setting

The proposed trial is a community-based, 12-month, open label, two-arm cRCT with an equal allocation of clusters (geographical wards) between intervention and control arms in a semi-urban area of Pokhara Metropolitan city (former Lekhnath municipality, administratively divided in to 15 wards). It is one of the two areas where the Cervical Cancer Screening and Prevention (CCSP) pilot program was first initiated in Nepal. The total population of Lekhnath municipality is 59,498 (female 32,104 and male 27,394) with the total number of households being 14,958 as per the 2011 census [18]. Each ward will be considered as one cluster. Although the study area is composed of 15 clusters, only 14 will be selected for the cluster randomization (one cluster that is comparatively different from others in socio-demography and health service availability is excluded). Allocation of the clusters into intervention and control arms is described below. The study area is limited to health services comprising one recently upgraded 25-bedded hospital from a primary health care center, three health posts, and six urban health care centers. According to the District Public Health Office, Kaski in 2018, there were 123 FCHVs in the municipality.

### Participants

The populations targeted in our study area are women aged 30–60 years (the age range recommended for VIA screening in Nepal), listed in the Community-Based Intervention for Non-communicable diseases study for hypertension (COBIN-H) [7, 16]. We will invite all the selected women participants for a baseline survey. During the baseline survey, knowledge, attitude, and screening practice on cervical cancer will be obtained and eligible women will be invited to participate in the trial. The flow of trial participants is shown in Fig. 1, which includes the number of participants eligible, surveyed, excluded, recruited, randomized, and analyzed for the primary outcome. The SPIRIT checklist for this trial is provided as an Additional file 1.

**Fig. 1 Fig1:**
[figure not shown]
Planned flow chart of participants

### Recruitment

A sampling framework was adopted from the COBIN-H trial that has taken a population framework of all eligible participants from the voter list prepared by the Election Commission in 2017 [16]. As of 31 December 2018, all the women of age group 30–60 years were included in the study. Trained women public health professionals (data enumerators) will carry out a baseline survey. The data enumerators will receive 4 days of intensive training before data collection. The survey tool is adapted from a joint survey report of Family Health Division of Nepal’s Ministry of Health and United Nations Population Fund (UNFPA) [8, 19–21]. It includes questions on survey information, consent, socio-demographic information, questions related to sexual and reproductive health, health-seeking behavior, knowledge, attitude and cervical cancer screening practice, and sign and symptoms. The questionnaire was modified as per the Nepalese settings, translated to the Nepali language and back to English to ensure content validity. Baseline data will be used for possible confounder adjustment and stratification by effect modifiers. The data enumerators will identify eligible participants, ask about their willingness to participate in the cRCT, receive informed consent, and recruit in the trial. The required number of participants will be randomly selected from those willing to participate in the cRCT: FCHVs will visit each household, meet the selected participant, and obtain consent to participate in the trial.

### Randomization

Clusters will be randomly assigned to intervention and control areas using a 1:1 allocation ratio. Randomization will be done before the participants are recruited. Research teams responsible for identifying potential participants, obtaining consent, and recruiting trial participants will be blinded to the participants’ allocation status. The following steps will be taken to avoid selection bias during random allocation: (a) clusters will be randomized only after the baseline survey, (b) clusters will not be withdrawn from or added to the study, and (c) a statistician from abroad who is not familiar to the study will randomize the clusters.

### Inclusion and exclusion criteria

Women aged 30–60 years who are listed in COBIN-H and who indicated they planned to reside in a cluster in the study area for at least the next 12 months are eligible for inclusion in the baseline survey and for the invitation to participate in the study. Women who are severely ill, pregnant, less than 6 weeks after delivery, who are already diagnosed with cervical pre-cancer and cancer, with a history of total hysterectomy, as well as those who decline to participate in the study or unable to complete the interview, will be excluded from the study.

### Outcomes

#### Primary and secondary outcomes

The primary outcome of the study is percentage change in cervical cancer screening uptake from baseline to follow-up in the intervention group compared to the control group in a 12-month home-based health education intervention. The baseline survey will be conducted before the cluster randomization, and a follow-up survey of similar method will be conducted after 12-month intervention. The response of each participant for cervical cancer screening in the baseline survey and the follow-up survey will be compared to evaluate the percentage. In addition, FCHV will provide a referral slip to the participants in the intervention group (keeping a copy of the referral slip to submit to the field supervisor) during the home visit, which they take with them and submit to the health facility for VIA screening. The referral slip contains study code, name, age, address, and signature of both FCHV and the participant. FCHV will inform the participants about the health facility where the services are freely available. The key health personnel providing the VIA screening services are oriented about the study. Furthermore, confidentiality about the participants’ information will be maintained throughout the intervention. The field supervisor will collect the referral slip to confirm that the participants have received VIA screening and results from all the health facilities of the intervention ward as a reference to the participants’ response.

The secondary outcomes of the study are change in the level of knowledge and awareness among women on cervical cancer screening and prevention. The response of each participant for knowledge and awareness on cervical cancer screening in the baseline survey and the follow-up survey will be compared to evaluate the change using the validated questionnaire [19, 20].

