### Data analysis

STATA version 15 software (StataCorp, College Station, TX, USA) will be used for quantitative analysis following the Consolidated Standards of Reporting Trials (CONSORT) guidelines for cluster-randomized trials. Flowcharts (Fig. 1) will include the number of participants seen at each stage of the trial, eligible, randomized, and analyzed for the primary outcome. In the initial analysis, we will compare baseline characteristics of enrolled participants in the study arms and follow-up status. We will use mixed-effect logistic regression to compare between the groups as the outcome (the primary outcome would be the difference in the proportion of women who participate in the cervical cancer-screening program between intervention and control within 1 year). Comparison of the knowledge scores between baseline and follow-up, after 1-year intervention, will measure the knowledge level. Estimation will take into account the effect of potential confounders (age, ethnicity, education, parity, income, location, etc.).

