**Assessments:**							
*Baseline variable* *Socio-demographic (age, education, ethnicity, monthly income, marital status), pregnancy, sexual, and reproductive characteristics*	**x**						**X**
***Outcome variable*** *# of women screened for cervical cancer*	**x**						**X**

The protocol version number and date—V1, 28 December 2020.

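### The primary outcome is stated as a change from baseline in one section and as a between-arm difference within 1 year in another, and the two are not reconciled

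*Protocol article*

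**What the plan says.** The protocol article describes the primary outcome in four places.

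- **Primary and secondary outcomes:** "percentage change in cervical cancer screening uptake from baseline to follow-up in the intervention group compared to the control group". On how it is obtained: "The response of each participant for cervical cancer screening in the baseline survey and the follow-up survey will be compared to evaluate the percentage".
- **Data analysis:** "the difference in the proportion of women who participate in the cervical cancer-screening program between intervention and control within 1 year", compared by mixed-effect logistic regression. The listed adjustment variables are age, ethnicity, education, parity, income and location, with an open-ended etc. Neither baseline screening nor an arm-by-time term is named.
- **Abstract, Methods:** "the difference in percentage of cervical cancer screening uptake between the two study arms", with no time window and no baseline.
- **Background:** "the primary outcome of the study is to increase the cervical cancer-screening uptake in the study area", which is an aim and not a measure.

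Three other sections bear on the point. The Sample size section plans for a 10% increase over one year and does not say whether it is absolute or relative, or a change or a difference. The Inclusion and exclusion criteria exclude women with diagnosed cervical pre-cancer or cancer or a total hysterectomy, but not women who have already been screened. The Recruitment section says that baseline data may be used for confounder adjustment and for stratification by effect modifiers.

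**The concern.** A change from baseline compared between arms and a follow-up difference between arms are computed differently and can give different numbers from the same data. The article fixes the primary outcome more than once and in different terms. That is a conflict within the document, not a detail left for an analysis plan.

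The trial is open-label and rests on this one outcome. If the choice stays open until the data are in, the team could report the definition that gives the more favourable figure, and a reader could not tell which one was planned.

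**Working it through.** **1. The plan's own sample size**

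Stated inputs: 90% power, ICC 0.01, 20% loss, 7 clusters per arm, 49 women per cluster, total 690. As a check, 14 × 49 = 686, and 277 + 413 = 690. Alpha and the control rate are not stated. I assume two-sided 5% and try the uptake figures in the Background.

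Control 5.4%, intervention 15.4% (absolute +10 points):
- Unclustered n per arm, pooled two-proportion formula: 194.
- Women per cluster with k = 7: m = n(1 − ICC)/(k − n × ICC) = 194 × 0.99/(7 − 1.94) = 38.0.
- After 20% loss: 38.0/0.8 = 47.4 per cluster, or about 664 in total.
- Power with 49 × 0.8 = 39.2 completers per cluster (design effect 1 + 38.2 × 0.01 = 1.382): 0.907. With the 277/413 split: 0.904.

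A control rate of about 5.6–5.7% returns 49 per cluster. By the same method, power would be 0.98 at 1.5%, 0.96 at 2.8%, 0.80 at 10% and 0.63 at 20%. So the stated 90% fits an absolute 10-point follow-up difference at about 5–6% control uptake. Read as relative, a 10% increase from 5.4% would be only 5.94 − 5.4 = 0.54 points. No power is stated for a change-from-baseline contrast.

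**2. Same status variable, absolute scale**

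Difference of changes = (follow-up difference) − (baseline difference). Randomization makes the baseline difference zero in expectation. Its chance SD is

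sqrt( p(1 − p) × [ (1 + (m₁ − 1) × ICC)/277 + (1 + (m₂ − 1) × ICC)/413 ] ), with m₁ = 277/7 = 39.6 and m₂ = 413/7 = 59.

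The bracket is 1.386/277 + 1.58/413 = 0.00883.

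| Assumed baseline uptake | SD (points) | 95% range (points) |
|---|---|---|
| 1.5% | 1.1 | ±2.2 |
| 2.8% | 1.6 | ±3.0 |
| 5.4% | 2.1 | ±4.2 |

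The three rates are those quoted in the Background; 5.4% is for ages 30–65, the band closest to this trial's.

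**3. Different event counted**

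Assume that the survey records whether a woman was ever screened, that 20% were at baseline in both arms, that first screens occur in 10% versus 2% of the never-screened, and that rescreens occur in 30% versus 10% of the ever-screened.
- Change in ever-screened: 0.8 × 10% − 0.8 × 2% = 8.0 − 1.6 = 6.4 points.
- Screened within the year: (8.0 + 0.2 × 30%) − (1.6 + 0.2 × 10%) = 14.0 − 3.6 = 10.4 points.

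The arms are perfectly balanced at baseline, so this gap is not chance imbalance.

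**4. Relative or absolute change**

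Assume uptake goes from 8% to 20% in the intervention arm and from 4% to 10% in the control arm. The follow-up difference is 10 points and the difference of absolute changes is 12 − 6 = 6 points. The relative change is +150% in both arms, which would be no effect.

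The figures in steps 3 and 4 are illustrations, not predictions.

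**The case against.** The best defence is that comparing each woman's two answers is a natural way to find who was newly screened during the year. On that reading the Outcomes and Data analysis sections differ mainly over women screened before who are screened again. Randomization also makes the arms' baselines equal in expectation, and the Recruitment section already allows baseline adjustment, which points toward a follow-up comparison. The Abstract's difference in percentage and the between-arm reference effect in the Sample size section make a relative reading less likely.

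Much of this stands. A reader might infer that the two definitions are incompatible. The text does not support that: on the absolute scale with one status variable they target the same quantity. Nor do they always differ by the baseline imbalance alone; step 3 shows a gap with none.

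A reader might also infer that logistic regression is an error in itself, because it yields an odds ratio while the outcome is a difference in percentages. That does not follow. An absolute difference can be derived from the fitted model, and an analysis plan not shown here could specify how.

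What the defence does not remove is that no section says which definition governs, whether rescreening counts, or on which scale the change is measured. Table 2, which lists a count of women screened at enrolment and at close-out, fits either definition and settles nothing.

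**Conclusion.** The point holds as an unreconciled definition of the primary outcome. Where the two versions share a status variable and an absolute scale, the choice between them shifts the estimate by chance baseline imbalance, with an SD of about 1.1 to 2.1 points against a 10-point target. That rests on assumed baseline uptake of 1.5% to 5.4%, the stated ICC of 0.01 and the enrolled 277 versus 413 women. Where the versions count different events or use different scales, the gap depends on prior screening and rescreening rates that the article does not give, and it can be larger. The sample size supports reading the target as an absolute follow-up difference, but only if control uptake is near 5–6%, a rate that the article does not state as its design assumption.

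**What to change.** State one primary outcome, in the same words, in the Abstract, Outcomes, Sample size and Data analysis sections: the proportion of women screened at least once during the 12-month intervention period, compared between arms at follow-up as an absolute difference. Keep the 1-year window of the Data analysis section, give its start and end, and say explicitly whether a repeat screen in a previously screened woman counts. Describe the planned 10% as absolute percentage points.

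Enter baseline screening status, which the baseline survey already collects, as a covariate in the mixed-effect logistic model in place of a change score.

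Ask for the screening date in the follow-up survey in both arms. Table 2 places close-out over two further months after the three 4-month visit periods, so without a date later screens could be counted. Referral slips are issued only in the intervention arm and cannot supply the date for controls.

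The cost is minor rewording and one survey item, with no extra participants. The article puts completion of endpoint assessment at the end of August 2021 and its protocol version is dated 28 December 2020, so on those dates the change could be made before analysis.

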**Day 3**		
	Recording register	Explain the content of the recording register How to prepare and fill the recording register? Name, age, location of the participants and FCHV Submission of completed register to the research officer
	Pamphlet	Explain the content of the pamphlet How to stress the points in the pamphlet What to suggest to the participants who are not able to read the pamphlet?
	Referral card	Explain the content of the referral card How to fill the referral card? Name, age, location, and health facility address for referral Communication with the health facility
	Scenario planning	Role play
	Household selection and list preparation	Selection of the household for home visit according to FCHVs working area.

At the end of the training, FCHVs will assign the number of households that have to be visited based on the baseline survey. Participants in the intervention clusters will receive a 12-month, home-based, health education package administered by FCHVs in a household setting. FCHVs will visit each household, meet the selected participant, receive approval, and provide the health education. On average, one FCHV will meet 18 participants three times a year. FCHV will complete the three visits to provide health education even if the participants have already received VIA screening. During the visit, FCHVs will deliver the health education intervention, to encourage and empower women for cervical cancer screening uptake available free of cost at their local health facility. They will also conduct two reinforcement visits every 4 months from the first visit (three home visits in a year).

Health workers conducting cervical cancer screening at the local health facility in the intervention group will receive orientation about the study to make sure that the women attending the health facility receive screening. They will ensure that the equipment is functional and reagents are available, record information, provide psychosocial counseling to the case positives, and refer for further confirmation and treatment. The recorded information at the health facility will be tallied using the referral slip to confirm women’s participation for cervical cancer screening. The collected data will be kept strictly confidential and will only be accessed by the members of the trial team.

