Each participant is assigned an individual trial identification number, which is securely stored. The principal investigator reserves the right to the data set and could share upon reasonable request.

There will be no special criteria for discontinuing or modifying allocated interventions. Furthermore, the implementing community-based intervention for cervical cancer screening uptake will not require alteration to usual care pathways (including use of any medication) and will continue for both the trial arms.

A field supervisor will routinely visit each FCHV in order to maintain motivation and collection of records from the health facilities. The supervisor also provides ad hoc help to the FCHVs when needed during the intervention period. We will also use a supervision checklist to track and update the knowledge and skill levels of FCHVs as well as to ensure fidelity to the study protocol.

In the control clusters, participants will receive “usual care.” The usual care means the current health education and promotion practices for cervical cancer screening at the community level provided by the government health system. They will not receive further contact, information, or educational materials from FCHVs until the 12-month assessment.

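### Self-reported screening can be checked against slips and facility records in the intervention arm only, and the article does not say that such checks leave the survey outcome unchanged

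*Protocol article*

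**What the plan says.** The Outcomes section of the protocol article defines the primary outcome as "percentage change in cervical cancer screening uptake from baseline to follow-up in the intervention group compared to the control group". It names one source for both arms: "The response of each participant for cervical cancer screening in the baseline survey and the follow-up survey will be compared to evaluate the percentage". The follow-up survey is to use a method similar to the baseline survey.

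The same section then adds a second stream of information for one arm: "FCHV will provide a referral slip to the participants in the intervention group". The woman hands the slip in at the facility, and the field supervisor collects slips "to confirm that the participants have received VIA screening and results from all the health facilities of the intervention ward". The article calls this a reference for the woman's own answer.

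The Interventions section repeats the confirming purpose: "The recorded information at the health facility will be tallied using the referral slip to confirm" women's participation. It places the briefed staff in one arm: "Health workers conducting cervical cancer screening at the local health facility in the intervention group will receive orientation about the study". Of control women it says: "They will not receive further contact, information, or educational materials from FCHVs until the 12-month assessment".

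No slip, tally or register check is described for control women or control wards. The article does not say what happens when a slip or record disagrees with a survey answer, and the Data analysis section does not name the source of the outcome.

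**The concern.** The trial is open label. Intervention women are visited three times and encouraged to be screened, and are then asked whether they were. They may have more reason than control women to say yes. A record check is the natural safeguard, but it covers only one arm, so the between-arm difference in reporting error, which is what biases the comparison, cannot be estimated.

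A second risk lies in how the records are used. To confirm screening could mean a check alongside the survey answer, or a correction of it. If it means correction, errors are repaired in one arm and left in the other. Neither the mixed-effect model nor covariate adjustment removes misclassification that differs by arm.

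**Working it through.** **Inputs.**
- Planned effect 10%, read as 10 percentage points; ICC 0.01; seven clusters per arm; 20% loss; 49 women per cluster; total 690; 90% power (Sample size calculation).
- Control uptake: not given in that section. Assumed 5.4%, the highest of the three national figures in the Background (1.5%, 2.8%, 5.4%). Local uptake may differ, since the area hosted a screening pilot.
- Two-sided alpha 0.05: assumed.
- Accuracy of self-report: the article gives none. All sensitivity (Se) and specificity (Sp) values below are assumptions.

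**Step 1: the plan's own figure.** For 5.4% against 15.4% at 90% power, the pooled-variance formula gives n = 194 per arm before clustering. With seven clusters and design effect 1 + (m - 1) × 0.01, m = 194 × 0.99 / (7 - 194 × 0.01) = 192.06 / 5.06 = 38.0. After 20% loss, 38.0 / 0.8 = 47.4, so 48 per cluster, close to the stated 49 (49 × 14 = 686, against 690). With 49 × 0.8 = 39.2 women retained per cluster, power is 0.907. The match depends on the assumed rate: 2.8% would need 33.8 per cluster and 10% would need 75.8. This step only sets the scale; the point itself rests on the text.

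**Step 2: model.** For true uptake p, uptake by self-report is Se × p + (1 - Sp) × (1 - p). The baseline survey precedes cluster randomization, so its reporting error is equal between arms in expectation. What matters is the difference at follow-up.

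**Step 3: no true effect, p = 5.4% in both arms.** The scenarios rest on different premises and must not be added together.

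*A. Equal over-reporting in both arms, Se 100%, unconfirmed reports removed in the intervention arm only, records taken as complete.* The false difference is -(1 - Sp) × 0.946.

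| Sp | False difference |
|---|---|
| 99% | -0.95 points |
| 95% | -4.7 points |
| 90% | -9.5 points |

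*B. Over-reporting in the intervention arm alone, nothing corrected.* The false difference is rate × 0.946. A rate of 2% gives +1.9 points and 5% gives +4.7. Zero over-reporting among control women is the extreme case; only the excess in the intervention arm counts.

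*C. Record-confirmed screens that the survey missed are added in the intervention arm only, Se 90%.* The false difference is 0.10 × 5.4 = +0.5 points.

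The sign thus depends on which rule is applied and which arm misreports.

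**Step 4: true effect of 10 points, 5.4% against 15.4%, 39.2 women retained per cluster, Se 100%.**

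| Handling | Observed difference | Power |
|---|---|---|
| Accurate records, both arms | 10.0 points | 0.907 |
| Self-report, both arms, Sp 95% | 9.5 points | 0.76 |
| Unconfirmed removed in intervention arm only, Sp 99% | 9.05 points | 0.83 |
| Unconfirmed removed in intervention arm only, Sp 95% | 5.3 points | 0.35 |

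For the last row, control is 0.054 + 0.05 × 0.946 = 0.1013 and intervention is 0.154, a difference of 0.0527.

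**Step 5: completeness of the records.** Slips are gathered from facilities of the intervention ward. A woman screened elsewhere could go unconfirmed although her answer is true, so removing unconfirmed reports could also delete real screens. That would push scenario A further below zero.

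**The case against.** The strongest reply is that the outcome has one source. The Outcomes section rests uptake on the survey answer in both arms. The slips come as an addition and serve as a reference. Table 2 lists a single outcome row, assessed at enrolment and close-out, with no arm-specific source, and the analysis text gives the slips no role. A reader might infer from the one-sided slips that the primary outcome is measured differently by arm. The documents do not support that: the recorded value differs by arm only if slips or records override answers, and nothing says that they do.

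Three further replies have weight. First, a rule for disagreements is often left to the full protocol or analysis plan, neither of which is at hand; this stands for the rule. It does not stand for the data, because no analysis plan can supply control-arm records that are not collected. Second, over-reporting in an open-label education trial would exist without any slips, and the slips help by making it visible in the arm where it is most feared. That is right, and it means the slips do not cause this part of the problem; but a check in one arm cannot show the difference between arms. Third, the sizes rest on chosen accuracy values, on no control over-reporting in scenario B, and on a background figure for uptake. This also stands, so they are illustrations and not estimates.

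**Conclusion.** The point holds in a limited form. The primary outcome is self-report in both arms, but only intervention-arm answers can be checked against slips or facility records. Differential over-reporting therefore cannot be assessed, and any reclassification from the slips would correct one arm only.

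The direction and size of any bias are unknown. Under the stated assumptions, plausible inputs give false differences from about -4.7 to +4.7 points, against a planned 10. It would go too far to say that a bias of known sign is present, or that it is beyond repair: the article commits to no reclassification, and the missing control-arm look-up can be added. This is a cheap improvement worth making, not a defect that must be cured before the trial can be relied on.

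**What to change.** 1. State that the survey answer is the primary outcome in both arms, and that slips and facility records never reclassify it in one arm only. This is a change of wording.
2. Have the existing field supervisor, who already collects facility records for the intervention wards, check enrolled women in both arms by the same matching rule against the VIA registers of the facilities in the study area that offer VIA. The Study design and setting section lists one hospital, three health posts and six urban health care centers; which of these offer VIA has to be established. The look-up should not depend on a slip, since control women have none. Done once at close-out, it needs no contact with control women.
3. Report record-confirmed uptake by arm as a sensitivity outcome, beside agreement between records and answers in each arm.

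The cost is extra look-up work, mainly at facilities serving control wards, and some names that cannot be matched; these should be counted by arm. The Trial status section puts the end of endpoint assessment at August 2021, after the article's publication in January 2021, so the change could still be made when the article appeared. Step 1 alone prevents one-sided correction but leaves differential over-reporting unexamined; steps 2 and 3 address that.
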